## Abstract

**Background:**

Nonpharmacologic interventions, such as cognitive training or physical exercise, are effective in improving cognitive functions for older adults with mild cognitive impairment (MCI). Some researchers have proposed that combining physical exercise with cognitive training may augment the benefits of cognition. However, strong evidence is lacking regarding whether a combined therapy is superior to a single type of training for older adults with MCI. Moreover, which combination approach – combining physical exercise with cognitive training sequentially or simultaneously – is more advantageous for cognitive improvement is not yet clear. This proposed study is designed to clarify these questions.

**Methods/design:**

This study is a single-blinded, multicenter, randomized controlled trial. Eighty individuals with MCI will be recruited and randomly assigned to cognitive training (COG), physical exercise training (PE), sequential training (SEQ), and dual-task training (DUAL) groups. The intervention programs will be 90 min/day, 2–3 days/week, for a total of 36 training sessions. The participants in the SEQ group will first perform 45 min of physical exercise followed by 45 min of cognitive training, whereas those in the DUAL group will perform physical exercise and cognitive training simultaneously. Participants will be assessed at baseline, after the intervention, and at 6-month follow-up. The primary cognitive outcome tests will include the Montreal Cognitive Assessment and the color-naming Stroop test. Other outcomes will include assessments that evaluate the cognitive, physical, and daily functions of older adults with MCI.

**Discussion:**

The results of this proposed study will provide important information regarding the feasibility and intervention effects of combining physical exercise and cognitive training for older individuals with MCI.

**Trial registration:**

ClinicalTrials.gov Identifier: NCT02512627, registered on 20 July 2015.

## Background

Mild cognitive impairment (MCI) or minor neurocognitive disorder represents an intermediate stage between cognitive intactness and clinically diagnosed dementia [1, 2]. Although definite diagnostic criteria are lacking, individuals with MCI are characterized by self- or caregiver-reported memory and/or cognitive complaints, objective cognitive impairment, but independence in performing daily activities [1]. People with MCI can perform activities of daily living (ADLs) without assistance, but they appear to have a greater risk of falls and other adverse consequences [3].

Furthermore, MCI is a precursor of dementia or other severe cognitive disorders. The progression rate from MCI to dementia ranges from 10 to 15 % each year, and severe cognitive impairment or dementia will develop in more than 50 % of the MCI population within 5 years [1]. Therefore, providing early and appropriate interventions to individuals who manifest MCI may reduce the risk of adverse events, prevent cognitive decline, and ultimately, could decrease the burden of their caregivers and related medical expenses.

Clinical pharmacologic trials that used drugs to treat MCI have not been very successful [2, 4]. More encouraging results have been reported from nonpharmacologic treatments such as cognitive training or physical exercise [5, 6]. Cognitive training could enhance brain activation in the areas related to memory [5]. A systematic review has demonstrated that cognitive training programs have some positive effects on cognitive functions in older adults with and without MCI, especially on the specific tasks being practiced [7]. Physical exercise, on the other hand, had neuroprotective effects and lowered the risk of developing Alzheimer’s disease and related cognitive disorders [8]. A meta-analysis showed that in addition to health-related physical fitness and daily functions, physical exercise is favorable for unspecific cognitive abilities in older individuals with and without MCI [6]. It is thus suggested that physical exercise facilitates neuroplastic potential (e.g., neurogenesis) and that cognitive training induces positive neuroplastic changes for improving cognitive function [9].

Facilitation and guidance of neuroplasticity are two challenges of positive neuroplastic changes for cognitive gains. To overcome these two challenges, some recent studies have proposed that *combining physical exercise and cognitive training* may augment the intervention benefits on cognition for individuals with MCI [10, 11]. Animal studies have demonstrated that combining physical exercise and cognitive training promoted neurogenesis and angiogenesis, which resulted in greater cognitive improvement than exercise alone [12, 13]. Studies of community-dwelling older individuals without cognitive complaints found that combining physical exercise with cognitive training significantly improved memory and general cognitive functions compared with no intervention or a single type of training [10, 14].

Only a few studies have investigated the combined effects of physical exercise and cognitive training in people with MCI [15–18]. Barnes et al. recruited inactive older adults with cognitive complaints and found that the participants who received both aerobic exercise and mental activity training showed improvements in global cognitive function comparable to those who received a single mode (aerobic exercise only or mental activity only) of training [15]. Another study by Fiatarone Singh et al. [18] examined the sequential combination effects of progressive resistance training and cognitive training in older adults with MCI. Surprisingly and contrary to their initial hypotheses, the participants who received hybrid training improved *less* than those who participated in progressive resistance training alone or cognitive training alone [18].

Kounti et al. [16] and Suzuki et al. [17] designed specific therapeutic programs that combined physical and cognitive training in a dual-task format in which physical exercise and a cognitive task were performed simultaneously. Both studies found that the combined therapy induced significantly greater improvements on various cognitive functions in adults with MCI compared with the control groups that received health education programs [16, 17]. Another trial of dual-task training found that group-based training for 26 weeks improved global cognitive function in older adults with MCI compared with an exercise-only group, which highlighted the finding that group-based dual-task training enhanced global cognitive function [19].

As can be observed from this brief review, the treatment effects of combined physical exercise and cognitive training have varied across studies. The diverse treatment benefits could be attributed to different training approaches as well as to different combination methods – combining physical exercise and cognitive training sequentially or simultaneously – that are used in the studies. In addition, the control groups in those studies were not always dose-matched, did not involve active intervention, or were uneven (i.e., the study controlled for the exercise component but not the cognitive component). Hence, it is difficult to draw a consensus regarding (1) whether combining physical exercise and cognitive training is superior to a single mode of training for older individuals with MCI, and (2) which combination method (sequential versus simultaneous training) might result in better treatment outcomes.

Sequential training combines physical exercise and cognitive training sequentially. Studies conducted in rats/mice and in cognitively intact individuals have proposed that performing physical exercise before cognitive training may increase arousal level and thus facilitate cognitive task performance [20, 21]. Furthermore, physical exercise before cognitive training may enhance memory consolidation and influence the performance of memory retrieval [22, 23]. Winter et al. [24] examined the effects of a single bout of intense exercise on vocabulary learning and memory. The participants who engaged in intense exercise acquired the vocabularies 20 % faster than those who did not exercise or who engaged in low-intensity exercise. More interestingly, the intense exercise group also retained the vocabularies better than the control groups 1 week after the training [24]. Neurophysiologic measures revealed that exercise led to elevated levels of brain-derived neurotrophic factor and increased the cortical activation level of the prefrontal and occipital areas [20, 24], which are important for subsequent cognitive training.

In dual-task training, physical exercise and cognitive tasks are performed simultaneously. Dual tasking is one executive function that is especially important for ADLs. Recent studies revealed strong correlations between performance of ADLs and executive function in older adults [25]. Using functional near-infrared spectroscopy, Doi et al. found that increased prefrontal activation during dual tasking was correlated with executive functions in older adults with MCI [26]. Imaging studies in cognitively intact young and old adults also showed that behavioral improvement after dual-task training was associated with changes in prefrontal activation [27, 28]. The evidence from these studies suggests that an intervention using dual-task training could be a promising approach for individuals with MCI.

Behavioral and neurophysiologic evidence suggests that combining physical exercise and cognitive training sequentially or simultaneously has benefits on cognitive functions. However, strong evidence is lacking regarding which combination approach is more feasible, acceptable, and advantageous for older adults with MCI. This proposed randomized controlled trial is designed to address three specific aims: (1) to determine whether combined therapy, sequentially or simultaneously, is a feasible approach to train older adults with MCI, (2) to determine whether combined therapy can induce superior treatment outcomes compared with a single mode of intervention, and (3) to compare which combination approach – sequential or simultaneous – is more advantageous for improving cognitive functions, physical fitness, ADLs, and quality of life in adults with MCI.

## Methods/design

### Participants

We anticipate recruiting 80 participants from community facilities, day care centers, and nursing homes. The inclusion criteria are (1) men and women aged 60 years or older, (2) the ability to follow instructions, (3) objective cognitive impairment as measured by a Montreal Cognitive Assessment (MoCA) score < 26, (4) having self- or informant-reported memory or cognitive complaints, (5) the ability to perform ADLs, and (6) no diagnosed dementia [29]. Participants who have other neurologic disorders or an unstable medical condition (e.g., heart failure) that prevents them from performing physical exercise or cognitive training will be excluded. The participants will be randomly assigned to four groups: cognitive training (COG), physical exercise training (PE), sequential training (SEQ), and dual-task training (DUAL) groups. We specifically include the COG and PE groups as the “active control” groups to ensure that all participants can benefit from the study.

### Sample size estimation

No published study to date has compared the treatment effects of cognitive training, physical exercise training, sequential training, and dual-task training in older adults with MCI. Therefore, we estimated the sample size for the current study from the studies that compared sequential training or dual-task training with control intervention(s) in older adults with cognitive complaints [15–17]. Because our primary outcomes will include global cognitive function and executive function, we calculated the sample sizes on the outcomes that involve these cognitive aspects. Kounti et al. [16] found significant benefits of dual-task training on global cognitive function, as measured by the Mini-Mental State Examination (MMSE), in participants with MCI. Compared with the control intervention, the calculated effect size (Cohen’s *d*) was 0.63 for dual-task training [16]. Using G*Power software [30] with a power of 0.80 and a two-sided type I error of 0.05, the calculated total sample size for the current study will be 20 participants (i.e., 5 participants in each group). The study conducted by Suzuki et al. showed that compared with the control group, the multicomponent dual-task training group had greater improvement in MMSE after intervention [17]. Based on the calculated effect size for the MMSE (Cohen’s *d* = 0.45), we estimated the sample size for the current study will be 12 participants in each group. Barnes et al. investigated the treatment effects of a sequential combination of physical exercise and mental activity training and found significant benefits on the Useful Field of View (UFoV), a measure of executive function, in older adults with cognitive complaints [15]. We used the calculated effect size for the UFoV from Barnes’ study (Cohen’s *d* = 0.21) [15] to estimate a sample size of 32 participants in each group.

Similar to the study design conducted by Barnes et al. [15], we employ the active control groups (i.e., COG and PE groups) instead of a no-treatment or passive control group. On the other hand, the primary outcome measures used in the current study are closer to those used by Kounti et al. [16] and Suzuki et al. [17]. Hence, a mean value from the estimated sample sizes of the three studies was calculated, and we anticipated that recruiting 16 participants for each group should be sufficient for this proposed study.

The dropout rate in our pilot trial was approximately 20 % during the intervention period; hence, we plan to recruit 20 participants for each group resulting in a total sample size of 80 patients for four groups.

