This study is distinctive for comparing the treatment effects of various dose-matched interventions in older adults with MCI. Schaefer and Schumacher emphasized the importance of equal treatment time when designing a randomized controlled trial for older individuals with MCI [59]. This study has, therefore, designed a comprehensive assessment and intervention protocol to investigate the treatment effects of different combined therapies in people with MCI.

One big challenge that we may encounter for the study is the difficulty in recruiting participants and another is the ability to maintain those participants. Recruiting older adults who have some cognitive impairment, but do not have other neurologic or psychological disorders, could be very challenging. Those older individuals typically stay in their home community and maintain a fairly active life before they become too old to carry out household tasks. To address this problem, we will target older adults who are sent to community day care centers and some nursing homes that admit older individuals without caregivers. Furthermore, the older adults who agree to participate in the study may decide to discontinue from the program during the 36 training sessions. Dropping out of the intervention program may be due to personal reasons (e.g., falls, diseases, or low motivation) or family issues (e.g., moving, need to take care of their partner, or change in caregivers) that may prohibit them from continuing the study. We accounted for the dropout rate in the sample size estimation to ensure that we could reach sufficient power for the study.

The overall goal of this study is to compare the treatment effects of different combinations of physical exercise and cognitive training. The results of this study will be important for clinicians as well as family caregivers to select the most efficient and effective training approach to improve cognitive, physical, and daily functions in older individuals with MCI. Most importantly, the ultimate goal of these interventions is to enhance their ability to live independently and to improve their quality of life.

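### Global cognition is sized on dual-task effects against health education, so the claim that 16 per group is enough is unsupported for combined versus single-mode training

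*Protocol article*

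**What the plan says.** Aim 2, at the end of the Background, is "to determine whether combined therapy can induce superior treatment outcomes compared with a single mode of intervention". The single modes are the COG and PE arms. The Abstract describes cognitive training and physical exercise as effective for cognition in MCI.

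The Sample size estimation section works "with a power of 0.80 and a two-sided type I error of 0.05" and uses three effects:
- MMSE, first dual-task study: the effect size "was 0.63 for dual-task training", giving 5 per group.
- MMSE, second dual-task study: d = 0.45, giving 12 per group.
- UFoV, sequential-training study: d = 0.21, giving 32 per group.

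The Background reports that both dual-task studies found greater gains "compared with the control groups that received health education programs". The sample size section then says that, like the sequential-training study, "we employ the active control groups (i.e., COG and PE groups) instead of a no-treatment or passive control group". It observes that the trial's primary outcomes resemble those of the two dual-task studies more closely, averages the three sizes, and judges 16 per group adequate. With 20% dropout this becomes 20 per group, 80 in total. The Discussion adds that dropout was allowed for "to ensure that we could reach sufficient power for the study".

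**The concern.** An effect against health education measures the whole benefit of combined training. An effect against COG or PE measures only what combined training adds to a treatment that already works. Carrying 0.63 and 0.45 over unchanged assumes that COG and PE do no better for global cognition than health education, which conflicts with the Abstract.

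The article's own review of single-mode comparators is mixed. One combined-training study found "improvements in global cognitive function comparable to those who received a single mode" of training. A second found less improvement with the hybrid than with either component alone. A third, of dual-task training, "improved global cognitive function in older adults with MCI compared with an exercise-only group". None of these supplies a global-cognition effect to the calculation.

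This is distinct from the question of whether sample sizes should be averaged. For global cognition alone, 16 exceeds both 5 and 12 and so looks safe, but those two sizes answer a different comparison. At stake is the reading of the MoCA, one of two primary measures. If the stated power is taken at face value, a non-significant combined-versus-single result could be reported as showing no added benefit.

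**Working it through.** **1. The plan's own figure.** (5 + 12 + 32)/3 = 16.3, taken as 16. 16/(1 − 0.20) = 20 per group, and 4 × 20 = 80. This reproduces.

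**2. The test behind the component sizes.** The article names G*Power but gives neither the test nor a correlation. Assume a group-by-time interaction with k = 4 groups, m = 3 visits and f = d/2:
- λ = f²·N·m/(1 − ρ), df1 = (k − 1)(m − 1) = 6, df2 = (N − k)(m − 1), noncentral F, alpha 0.05.
- d = 0.45, N = 48: f² = 0.0506 and λ = 7.29/(1 − ρ). Power is 0.80 at ρ = 0.5015, which returns 12 per group.
- d = 0.63, N = 20: f² = 0.0992 and λ = 5.95/(1 − ρ). Power is 0.80 at ρ = 0.639, which returns 5 per group.
- ρ = 0.70 returns 5, 8 and 32 per group for d = 0.63, 0.45 and 0.21.

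No single setting tried returns 5, 12 and 32 together, so ρ is unknown and is varied below.

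**3. Discounting for an active comparator.** If single-mode training delivers a share s of the combined benefit, the remaining effect is (1 − s)d. The article does not give s; 25 to 75% is an assumed range. At 16 per group, N = 64 and df2 = 120. Example: d = 0.45 and s = 50% give f = 0.1125, λ = 0.01266 × 64 × 3/0.4985 = 4.87 and power 0.311.

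| Source effect | ρ | s = 25% | s = 50% | s = 75% |
|---|---|---|---|---|
| d = 0.45 | 0.5015 | 0.665 | 0.311 | 0.101 |
| d = 0.45 | 0.70 | 0.898 | 0.512 | 0.142 |
| d = 0.63 | 0.639 | 0.990 | 0.759 | 0.214 |
| d = 0.63 | 0.70 | 0.998 | 0.845 | 0.255 |

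With no discount, d = 0.45 at ρ = 0.5015 gives 0.92. Of the twelve cells, four reach 0.80 and seven exceed 0.50.

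**4. What 16 evaluable per arm can detect.** Two-sample t test, df = 2n − 2, noncentrality d√(n/2), 80% power, two-sided 0.05:
- One arm against another, 16 v 16, unadjusted: 1.02 SD.
- SEQ + DUAL against COG + PE, 32 v 32, unadjusted: 0.71 SD.
- The same pooled contrast with baseline adjustment (R² = 0.25, assumed): 0.711 × √0.75 = 0.62 SD.

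**The case against.** The authors did not overlook the issue. They say that no study had made this four-arm comparison, point out that their controls are active, bring in the sequential-training study for that reason, and settle on a number above both health-education sizes. That stands as partial recognition. It does not supply a combined-versus-single effect on global cognition: the added study contributes a UFoV effect, a secondary outcome here, and the article does not say which comparator that d refers to. Similar outcome measures do not make up for a different comparator.

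The power figures rest on a fitted correlation and an assumed retained share. That also stands, so they illustrate and do not estimate.

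A reader might infer that 16 per group has been shown to be inadequate, or that a null result is likely. The documents support neither, since several scenarios in the table exceed 0.80. A pooled 32 v 32 comparison at the undiscounted d = 0.63 with R² = 0.25 also gives 0.82.

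A reader might also set 0.92 for the interaction test against 0.43 for a pooled, unadjusted t test at d = 0.45 and blame the comparator. That drop comes from changing the test; d is the same in both. Nor is the pooled contrast planned: the Data analysis section specifies a four-group repeated-measures ANOVA.

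Finally, the cited single-mode studies cannot simply replace the two dual-task effects. The article gives no global-cognition effect size for any of them, and it describes two as showing comparable or smaller gains with combined training.

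**Conclusion.** The concern holds in a limited form. The comparator mismatch is plain from the text and needs no calculation: the only global-cognition effects in the sizing are against health education, while aim 2 is against active single-mode training. The adequacy statement at 0.80 power is therefore unsupported for combined versus single-mode global cognition. It is not refuted for every effect, and the documents do not allow the shortfall to be estimated. Under the assumed test and a retained share of 25 to 75%, power at 16 per group runs from 0.101 to 0.998, so the conclusion depends almost entirely on quantities the article does not give.

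**What to change.** Keep 80 participants and change the wording.

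1. In Sample size estimation, state that the 5 and 12 per group apply to a health-education comparator and do not support aim 2.
2. Replace the judgement that 16 per group is adequate with the difference detectable at 80% power, two-sided 0.05: about 1.02 SD for one arm against another (16 v 16, unadjusted). If a pooled SEQ + DUAL versus COG + PE contrast is specified, add about 0.71 SD unadjusted, or 0.62 SD with baseline adjustment (R² = 0.25, labelled as an assumption). Say that this contrast is additional to the planned four-group ANOVA.
3. Qualify the power statement in the Discussion to match: the dropout allowance protects the 16 per group, but does not establish power for aim 2.
4. State that a non-significant combined-versus-single result will not be read as equivalence.

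The cost is a few sentences and a less favourable stated power. No extra participants or procedures are needed.

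### The target of 16 per group is a mean of three required sample sizes, so sufficient power is not supported for executive function, and SEQ v DUAL (aim 3) is not sized at all

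*Protocol article*

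**What the plan says.** The section Sample size estimation in the protocol article names global cognitive function and executive function as the domains of the primary outcomes. It works in G*Power "with a power of 0.80 and a two-sided type I error of 0.05" and takes one effect size from each of three source trials:

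- Dual-task training, MMSE: Cohen's d "was 0.63 for dual-task training", from which "the calculated total sample size for the current study will be 20 participants (i.e., 5 participants in each group".
- Multicomponent dual-task training, MMSE, d = 0.45: "we estimated the sample size for the current study will be 12 participants in each group".
- Sequential exercise and mental activity, UFoV, d = 0.21, used "to estimate a sample size of 32 participants in each group". This is the only executive-function input.

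The section gives a reason for combining them. The active-control design resembles the UFoV trial, while the primary outcomes are closer to those of the two MMSE trials. So the three sizes are averaged: "a mean value from the estimated sample sizes of the three studies was calculated". The article's conclusion from this average is that "we anticipated that recruiting 16 participants for each group should be sufficient for this proposed study". Allowing for about 20% dropout gives 20 per group and 80 in total. The Discussion adds: "We accounted for the dropout rate in the sample size estimation to ensure that we could reach sufficient power for the study".

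Under Outcome measures, the MoCA and the color-naming Stroop test are primary and UFoV is secondary. The last paragraphs of the Background make the comparison of sequential with simultaneous training the third specific aim.

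**The concern.** Each of the three sizes answers its own question: how many participants give 80% power for this effect? Their mean answers none of them. It gives more than 80% power where the requirement was smaller and less than 80% where it was larger. If two sources each apply in part, that may be a reason to choose or average an effect size and then compute n. It is not a reason to average the n's.

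The averaging costs most in the executive-function domain, where the required size was largest and which the plan counts as primary. The source for that size is also the trial whose active-control design the article says is most like its own. According to the Background, the two trials behind 0.63 and 0.45 compared against health education.

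Aim 3 has a separate gap. All three inputs are effects of combined training against a control intervention. None describes one combined arm against another, so the statements of sufficiency do not reach that comparison.

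If those statements stand, a null Stroop result or a null SEQ v DUAL result could be taken as evidence of no difference, when the trial had limited ability to find one.

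**Working it through.** **Inputs from the protocol article.** Two-sided alpha 0.05; power 0.80; d = 0.63, 0.45, 0.21; stated sizes 5, 12, 32 per group; four equal groups; dropout about 20%. The article does not state the test family, the number of visits, the pre-post correlation or a SEQ v DUAL effect size. Values used below for these are assumptions.

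**1. The plan's own figure reproduces.** (5 + 12 + 32)/3 = 16.33, taken as 16. 16/0.80 = 20 per group, and 4 × 20 = 80.

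**2. Target against each requirement.** 16 > 5 and 16 > 12 (global cognition). 16/32 = 0.50 (executive function).

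**3. Power for d = 0.21 at 16 per group.** Take a set-up that returns 32 per group and lower the n. Example: group-by-time interaction, 4 groups, m = 3 visits, correlation ρ = 0.7, f = d/2 = 0.105. The noncentrality is λ = f²·N·m/(1 − ρ), with 6 and 2(N − 4) degrees of freedom.

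| N | λ | Power |
|---|---|---|
| 128 (32 per group) | 0.011025 × 128 × 3/0.3 = 14.11 | 80% |
| 64 (16 per group) | 0.011025 × 64 × 3/0.3 = 7.06 | 45% |
| 80 (20 per group) | 0.011025 × 80 × 3/0.3 = 8.82 | 56% |

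Across the other between, within and interaction set-ups that return about 32 per group, the range is about 44-52% at 64 and about 54-62% at 80. The same set-ups give about 99% at 64 for d = 0.45, so on these terms global cognition is not short.

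**4. Do 5, 12 and 32 share one method?** Under a common method, n per group varies roughly as 1/d². From d = 0.45 to 0.21 it should rise (0.45/0.21)² = 4.6-fold; the stated rise is 32/12 = 2.7-fold. No single set-up searched gives all three. Those that give 5 and 32, including the example above, give 8 for d = 0.45. Different correlations for different source trials would explain the gap. With 4 groups, 2 visits, the interaction test and f = d/2, ρ = 0.75 gives 5 and 32, and ρ = 0.60 gives 12.

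**5. SEQ v DUAL at 16 v 16.** Two-sided 5% t test with noncentrality δ = d·√(16 × 16/32) = 2.83d. With a baseline covariate at correlation r, d becomes d/√(1 − r²).

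| Assumed r | d = 0.63 | d = 0.45 | d = 0.21 |
|---|---|---|---|
| unadjusted | 41% | 23% | 9% |
| 0.5 | 51% | 30% | 10% |
| 0.7 | 67% | 41% | 13% |
| 0.8 | 82% | 54% | 16% |
| 0.9 | 98% | 81% | 26% |

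The difference detectable with 80% power is about 1.02 SD unadjusted, and 1.02 × √(1 − 0.49) = 0.73 SD at r = 0.7. An unadjusted two-group comparison at 80% power would need 41, 79 and 357 per group for the three effects. No multiplicity adjustment is applied; one would lower these powers.

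**The case against.** The strongest reply is that the article explains why it did not simply use 32. Its primary outcomes are closer to those of the two MMSE trials, and UFoV is only a secondary outcome here. The executive-function primary is the Stroop test, for which no effect size is given. This stands in part: the 32 is a requirement for a proxy. It is still the only executive-function figure in the plan, and the plan chose it for that purpose.

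Other points on that side also limit what can be said:

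- A reader might infer that the whole trial is underpowered. The documents do not support that, because 16 exceeds both stated sizes for global cognition.
- A reader might infer that the plan promises 0.80 power for SEQ v DUAL. It does not. The 0.80 is an input to the three component calculations, and the later statements speak of sufficiency only in general terms.
- A reader might infer that the 12 is an arithmetic error. That is not shown. The article does not say that one set-up was used, and trial-specific correlations could make all three figures valid.
- The aim 3 powers depend on a correlation that the article does not give, and a high one changes the picture for the larger effects.
- Intention-to-treat is named for missing data, so more than 64 participants may be analysed. Even with all 80, power at d = 0.21 stays at about 54-62%.
- No text plans to claim equivalence from a null result, and effect sizes are to be reported beside p values. The risk of misreading is a possibility, not a stated intention.

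**Conclusion.** The concern holds for the averaging and for what is concluded from it. The shortfall for executive function follows from the article alone: it computes 32 per group for 80% power and plans 16. Its size, roughly half power with 64 completers, rests on set-ups that reproduce the 32 and on taking the UFoV effect as a stand-in for the Stroop test. The sufficiency statements in Sample size estimation and the Discussion are therefore unsupported for that domain. They are not contradicted for global cognition.

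For SEQ v DUAL, the firm point is that no calculation addresses it. At the plan's own effect sizes, power reaches 80% only for d = 0.63 with r about 0.8, or d = 0.45 with r about 0.9. Effects against control may be generous for two active combined arms.

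The 5, 12 and 32 are not consistent with any single set-up tried. That calls for disclosure of the inputs, not for a ruling on which figure is wrong.

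**What to change.** Keep 80 participants and revise the text:

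- Delete the averaging rationale.
- Replace both sufficiency statements with the power that 64 completers deliver for each primary domain, naming the test, effect size and correlation assumed. For d = 0.21 that is about 44-52% in set-ups matching the stated 32.
- State the detectable SEQ v DUAL difference: about 1.02 SD unadjusted, about 0.73 SD at r = 0.7.
- Give the test, number of visits and correlation behind each of 5, 12 and 32, and so explain or correct the 12.
- Say that a null Stroop or SEQ v DUAL result will not be read as evidence of no difference.

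Relabelling executive function or aim 3 as estimation only is not needed for this. It would change the status of a primary outcome and of a specific aim after 39 participants have been recruited, so it would be a separate decision.

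The cost is wording and a short recalculation, with no extra participants. The downside is that the stated power becomes less favourable.
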